## *Synopsis*

### *Background*

In people with type 2 diabetes, microalbuminuria is a strong, independent risk factor for diabetic nephropathy and cardiovascular morbidity and mortality. In a recent large scale clinical trial [BERgamo NEphrologic Diabetes Complication Trial (BENEDICT)] ACE inhibitor therapy decreased the risk of microalbuminuria in hypertensive subjects with type 2 diabetes and normoalbuminuria by about 40%. Available data suggest that angiotensin II receptor blockers (ARBs) might have a similar renoprotective effect and that this effect might be increased by combined ACE inhibitor therapy.

### *Objectives*

The study will evaluate the effects, at similar blood pressure control (systolic/diastolic <130/80 mmHg), of dual renin-angiotensin-system (RAS) blockade by benazepril and valsartan combination therapy as compared to single RAS blockade by benazepril or valsartan alone on microalbuminuria and cardiovascular events in high-risk patients with type 2 diabetes and no evidence of renal disease. The relationships between albuminuria and cardiovascular outcomes will also be evaluated.

### *Methods*

This will be a multicenter, Prospective, Randomized, Open label, Blinded End point (PROBE) trial of at least 3-year treatment with halved doses of benazepril (10 mg/day) and valsartan (160 mg/day) given in combination, or full doses of both benazepril (20 mg/day), or valsartan (320 mg/day) given alone in 564 consenting patients >40 year old, with type 2 diabetes (WHO criteria), serum creatinine  $\leq 1.5$  mg/dl, high-normal albuminuria (UAE  $\geq 7$  and  $< 20$   $\mu\text{g}/\text{min}$  in at least 2 of 3 overnight urine collections), and no specific contraindications to the study drugs. Primary outcome variable will be microalbuminuria (UAE  $\geq 20$   $\mu\text{g}/\text{min}$  in at least 2 of 3 overnight urine collections in two consecutive visits 2 months apart) and primary comparison will be between the combined benazepril plus valsartan and the benazepril alone groups. The analysis will have an 80% power to detect ( $\alpha=0.05$ , two-side test) a 40% difference in the incidence of microalbuminuria.

### *Expected results*

The study is expected to show a more effective prevention of microalbuminuria and cardiovascular events with combined than with single drug ACE inhibitor or ARB therapy. As compared to ACE inhibitor, ARB therapy is expected to have a similar effect on microalbuminuria, but an inferior cardioprotective effect. Applied to clinical practice, the findings should help preventing renal and cardiovascular complications, and related treatment costs, of type 2 diabetes.

## BACKGROUND

Nephropathy of type 2 diabetes is the leading cause of end stage renal disease (ESRD) (1). Currently, more than 50% of patients on renal replacement therapy in the US are diabetics. The yearly incidence of diabetics progressing to ESRD and the proportion of ESRD patients with diabetes is progressively increasing due to the ongoing epidemic of type 2 diabetes. According to the World Health Organization (WHO), diabetes affects over 170 million people, and, due to progressive ageing of the population, life-style modifications and increasing burden of obesity, this number is expected to rise to 370 millions by 2030 (2). About one third of those affected will eventually have progressive deterioration of renal function (1). Untreated, these patients progress to ESRD within 10 years or die prematurely because of cardiovascular complications (that are 10-fold more frequent in diabetics with nephropathy than in those without and the general population) (1). Costs for renal replacement therapy of these patients – and for treatment of related complications - are also progressively increasing. Where renal replacement therapy is available only for a small minority of subjects, these patients already die because of uremia.

The first clinical sign of renal dysfunction in diabetic patients is persistent microalbuminuria (3) which develops in 2 to 5 percent of patients per year (4,5) and progresses to overt proteinuria in 20 to 40 percent of cases (6-7). In 10 to 50 percent of patients with proteinuria, chronic kidney disease develops that ultimately requires dialysis or transplantation (8-10). Of great concern, 40 to 50 percent of type 2 diabetic patients with microalbuminuria eventually die of cardiovascular disease (6,11,12). This is three times as a high rate of death from cardiac causes as among patients who have diabetes but have no evidence of renal disease (5). Thus, preventing (or delaying) the development of microalbuminuria is a key treatment goal for renoprotection and, possibly, for cardioprotection.

A small study found that the ACE inhibitor enalapril decreased the incidence of microalbuminuria in patients with type 2 diabetes and normal blood pressure, as compared with placebo (13). This study, however, included only non obese subjects. Most important, the blood pressure was lower in patients on enalapril than in those on placebo throughout most of the study period and the study was underpowered to evaluate whether the effect of enalapril in preventing microalbuminuria was explained by ACE inhibition or, rather, by more effective blood pressure control. More recently, the BErgamo NEphrologic DIabetes Complications Trial (BENEDICT) found that treatment with the ACE-inhibitor trandolapril (either alone or combined to the calcium channel blocker verapamil) significantly reduced the incidence of microalbuminuria in 1204 patients with type 2 diabetes and hypertension, but normal urinary albumin excretion, as compared with placebo (14). The effect of preventing microalbuminuria exceeded expectations based on changes in blood pressure alone and was not enhanced by combined calcium channel blocker therapy.

Large-scale randomized trials evaluating the effects of angiotensin receptor blockers (ARBs) on the incidence of microalbuminuria in type 2 diabetic patients with normal urinary albumin excretion rate are missing. However, studies in patients with type 2 diabetes and micro- (15) or macro- (8,9) albuminuria clearly show that ARBs may shear with ACE inhibitors a similar renoprotective effect in this typology of patients. Indeed, ARBs decreased the incidence of macroalbuminuria in patients with microalbuminuria (15), and slowed the progression to ESRD in those with macroalbuminuria at study entry (8,9). Whether the beneficial effect against the development of microalbuminuria is enhanced when ACE inhibitors and ARBs are given in combination is not established so far. However, finding that combined ACE inhibitor and ARB therapy more effectively than single drug RAS blockade reduced albuminuria (16) or proteinuria (17) in subjects with type 2 diabetes and slowed progression to ESRD in those with non-diabetic chronic nephropathies (18), suggests that the renoprotective effect of combined therapy could be superior to that of single drug blockade of the RAS also in diabetic patients with no evidence of renal disease.

A randomized trial powered to detect a reduced incidence of microalbuminuria with combined ARB and ACE inhibitor therapy as compared to ACE inhibition or ARB alone would require several thousands of patients. However, identifying high risk patients who may benefit the most of nephroprotective therapy would allow to design an adequately powered trial with remarkably less patients. Post hoc analyses of the BENEDICT trial (14) found that high-normal albuminuria at baseline evaluation (defined as a urinary albumin excretion rate between 7  $\mu\text{g}/\text{min}$  and the upper limit for study entry: 19  $\mu\text{g}/\text{min}$ ) was the strongest baseline predictor of subsequent development of microalbuminuria. Indeed, regardless of treatment randomization, 86 of 441 (19.5%) patients with high-normal albuminuria (urinary albumin excretion  $\geq 7\mu\text{g}/\text{min}$ ) progressed to the end point as compared to only 15 of 763 (2.0%) with low-normal albuminuria ( $<7\mu\text{g}/\text{min}$ ). Thus, large-part of the excess risk for microalbuminuria observed in people with type 2 diabetes is associated with high-normal albuminuria.

Thus, whether dual more than single drug RAS blockade reduces the incidence of microalbuminuria in patients with type 2 diabetes and high normal albuminuria, and whether ACE inhibitors shear with ARBs a similar beneficial effect in this typology of patients is worth investigating. In addition, this clinical trial might have a clinical relevance for the Italian National Health service (SSN): 1. Effective prevention of microalbuminuria in people with type 2 diabetes is expected to translate into a remarkable reduction in subsequent development of overt nephropathy and progression to ESRD, as well as in the excess cardiovascular morbidity and mortality associated with microalbuminuria. 2. A better definition of the cost/effectiveness profile of different study treatments may help optimizing the allocation of available resources in order to achieve more effective prevention at lower costs and at third identifying subjects at increased risk that may benefit the most of intensified treatment, should translate in a further optimization of the use of available resources at population level. Moreover the present study will allow us to compare the

renoprotective effects of equivalent doses of ACE inhibitors or ARBs. Indeed trials formally comparing the effects of these two drugs in people with type 2 diabetes and overt nephropathy are missing so far. A non-inferiority study in type 2 diabetics with micro- or macro-albuminuria found a more consistent GFR reduction over 5 year follow up in patients on ARB than in those on ACE inhibitor therapy (19). However, since the observed difference was inferior to the difference *a priori* considered as statistically significant, it was concluded that ARB therapy was not inferior to ACE inhibitor therapy in providing long-term renoprotection in persons with type 2 diabetes. On the other hand, on the basis of results of available trials in type 2 diabetic patients with micro- or macroalbuminuria (8,9,15), ARBs are currently claimed as first line therapy for people with diabetes and, despite the higher costs, are progressively replacing ACE inhibitors in clinical practice. However, whether this is effectively the intervention strategy with the highest benefit for the patient and the best cost/effectiveness profile for the National Health Care System, remains elusive.

## **AIMS**

### ***Primary***

To evaluate whether, at comparable blood pressure control, dual RAS blockade with combined therapy with halved doses of benazepril (10 mg/day) and valsartan (160 mg/day) reduces the incidence of microalbuminuria more effectively than single drug RAS blockade by full doses of benazepril (20 mg/day) given alone in high-risk patients with type 2 diabetes, hypertension and high normal albuminuria.

### ***Secondary***

- To evaluate whether, at comparable blood pressure control, dual RAS blockade with combined therapy with halved doses of benazepril (10 mg/day) and valsartan (160 mg/day) reduces the incidence of microalbuminuria more effectively than valsartan (320 mg/day) given alone in high-risk patients with type 2 diabetes, hypertension and high normal albuminuria.
- To evaluate whether, at comparable blood pressure control, the effects of benazepril and valsartan therapy are similar or whether, alternatively, one of the two treatments offer a superior protective effect against the development of microalbuminuria in the above study population.
- To evaluate the effects of the three study treatments on the incidence of fatal and non-fatal cardiovascular events, regression to low-normal albuminuria (urinary albumin excretion  $<7\mu\text{g/min}$ ), albuminuria (considered as a continuous variable), serum creatinine, lipid profile, and GFR (in a representative subgroup);
- To assess the relationships, in the study group as a whole and within each treatment group, between renal outcome variables (including microalbuminuria and time-dependent changes in albuminuria) and fatal and non-fatal cardiovascular events, between achieved blood pressure or metabolic control and

renal and/or cardiovascular outcome variables and between achieved albuminuria reduction or residual follow-up albuminuria and renal and/or cardiovascular outcome variables.

## **PATIENTS**

Patients will be identified among the subjects who are referred to the Clinical Research Center for Rare Diseases Aldo & Cele Daccò of the Mario Negri Institute for Pharmacological Research and to the Diabetology Units of the Centers involved in the study. The Coordinating Center will include and randomize 300 patients.

### *Inclusion criteria*

- Males and females >40 years old;
- High-risk subjects with type 2 diabetes (WHO criteria);
- History of diabetes not exceeding 25 years;
- High blood pressure (systolic and/or diastolic blood pressure >135/85 mmHg or concomitant treatment with blood pressure lowering medications);
- Serum creatinine concentration <1.5 mg/dl;
- Overnight urinary albumin excretion (in at least 2 of 3 consecutive overnight urine collections)  $\geq 7$  and <20  $\mu\text{g}/\text{min}$ ;
- Legal capacity;
- Written informed consent.

### *Exclusion criteria*

- Uncontrolled diabetes (glycated hemoglobin >11%);
- Specific contraindications or history of hypersensitivity to the study drugs;
- Serum potassium  $\geq 5.5$  mEq/L despite diuretic therapy, and optimized metabolic and acid/base control;
- Bilateral renal artery stenosis;
- Previous history of allergy or intolerance, or evidence of immunologically-mediated renal disease, systemic diseases, cancer;
- Drug or alcohol abuse;
- Any chronic clinical conditions that may affect completion of the trial or confound data interpretation;
- Pregnancy or lactating;
- Women of childbearing potential without following a scientifically accepted form of contraception;
- Legal incapacity and/or other circumstances rendering the patient unable to understand the nature, scope and possible consequence of the trial;
- Evidence of an uncooperative attitude;
- Any evidence that patient will not be able to complete the trial follow-up.

## **RANDOMIZATION**

Randomization will be centralized at the Laboratory of Biostatistics of the Clinical Research Center for Rare Diseases “Aldo e Cele Daccò” [name] of the Mario Negri Institute for Pharmacological Research under the responsibility of an independent investigator. Randomization will be stratified in blocks by center. The block size will randomly vary in order to increase the unpredictability of the sequence.

## **STUDY DRUGS**

Study drugs (benazepril: 5 - 10 mg tablets; valsartan: 80 - 160 mg capsules) will be manufactured by Meda Pharma SpA ([name]) and Novartis Farma SpA ([name]), respectively.

Boxes will be labeled with “tear-off” labels. When administering the study medication, the Investigator will peel off the respective part of the label from the each box and will fix these to the provided space in the appropriate form.

All medication supplies must be stored separately from normal hospital/practice stocks. The study medication can remain below 30°C.

The Investigator or the hospital pharmacist will confirm receipt and disposition of the study drug in writing, including all following supplies. Unused drug has to be returned to the MNI. The Investigator will administer the study drug only to the patients included in the trial by following the procedures set out in the study protocol. It is prohibited to use the trial drug for any other purpose.

## **STUDY DESIGN AND TREATMENT**

This will be a Prospective, Randomized, Open label, Blinded End point (PROBE) trial (20) of 3-year treatment with the ACE inhibitor benazepril and the ARB valsartan given alone or in combination. After one month wash-out from previous RAS (ARB or ACE) inhibitor therapy, patients satisfying the inclusion/exclusion criteria will be randomly given equivalent doses (half the standard doses recommended by the manufacturer for blood pressure control) of benazepril (10 mg/day) or valsartan (160 mg/day) or one fourth of the standard doses of both agents in combination (benazepril 5 mg/day and valsartan 80 mg/day). Blood pressure, serum creatinine, serum potassium, blood glucose and venous pH will be monitored within 7-10 days after randomization. If well tolerated, treatment will be up-titrated to full dose of benazepril (20 mg/day) or valsartan (320 mg/day) or one half of the standard doses of both agents in combination (benazepril 10 mg/day and valsartan 160 mg/day). Blood pressure, serum creatinine, serum potassium, blood glucose and venous pH will be monitored within 7-10 days after up-titration of the study treatments. Target blood pressure will be 130/80 mmHg in all treatment groups. Additional treatment with thiazide or loop diuretics (first step),

beta and/or alpha blockers or clonidine (second step) and vasodilators such as dihydropyridine calcium channel blockers or minoxidil (third step) will be allowed to achieve and maintain the target blood pressure. Back titration of concomitant treatments and, secondarily, of the study drugs will be allowed to avoid symptomatic hypotension or severe hyperkalemia (serum potassium  $\geq 5.5$  mEq/L despite diuretic therapy, and optimized metabolic and acid/base control). If the above clinical or laboratory abnormalities will not recover despite back-titration, the study drugs will be withdrawn. The patients will be monitored until full recovery of the event and, however, for at least two weeks and then withdrawn from the study. The general aim will be to maintain the target blood pressure with the highest dose of the study drugs and the lowest doses of the concomitant medications. Potassium sparing diuretics, aldosterone antagonists and RAS inhibitors different from the study drugs will not be allowed. Diet, antidiabetic and statin therapy will also target at optimized metabolic (HbA1C $<7\%$ ) and lipid (total cholesterol  $<200$  mg/dL) control in all patients.

Glycated hemoglobin, lipids, the glomerular filtration rate (GFR, in a subgroup), and routine clinical and laboratory parameters will be evaluated at randomization, 3 and 6 months after randomization and every 6 months up to study end. The measurements of albuminuria (by nephelometry) and GFR [by iohexol plasma clearance (21)] will be centralized at the laboratory of our Clinical Research Center. This laboratory already served for centralized measurements of GFR [by a technique that has been set up by the head of the laboratory (21)] in previous multicenter, randomized trials in non-diabetic renal disease (22-24) and for all routine laboratory tests including albuminuria, lipids, hematochemistry, blood cell counts in a previous large scale, multicenter, randomized trial in patients with type 2 diabetes (14), as well as in other ongoing clinical trials in a similar typology of patients. All the investigators involved in laboratory measurements will be blinded to the treatment assignments of the subjects.

All clinical and laboratory parameters as well as any serious and non serious adverse event will be recorded throughout the study for safety analyses.

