### *Safety variables*

They will include serious and non-serious adverse events and any clinical or laboratory abnormality (such as acute hypotension, cough, acute renal function deterioration or hyperkalemia) possibly related to the study drugs.

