### **SAMPLE SIZE**

Primary efficacy comparison will be between combined ACE inhibitor plus ARB therapy and ACE inhibitor alone. On the basis of the outcome data of the BENEDICT study (14) and the first interim analysis 6% of patients with high normal albuminuria are expected to progress to microalbuminuria every year. It is predicted that at the time the last randomized patient will have completed the planned 3-year treatment period (study end), the median follow-up of the whole study group will approximate 4.5 years. Thus, assuming a 6% yearly incidence of microalbuminuria and a 4.5-year follow-up, 27% of patients in the ACE inhibitor group are predicted to develop microalbuminuria throughout the study period. Similar figures are expected for patients in the ARB group. On the basis of preliminary evidence in type 2 diabetes (10) this figure is, conservatively, predicted to decrease by 45% (from 27% to 14.85%) by combined therapy. To give the trial an 80% power to detect by a two-side test with a type 1 error of 5% the expected reduction in microalbuminuria events, 179 patients per group should complete the study. Thus, to account for a 5% drop-out rate, 188 patients per group should be included for a total of 564 patients. Assuming a similar incidence of events in the ACE inhibitor and ARB groups, this sample size should provide adequate power to detect a difference, if any, also between the combined and the ARB inhibitor treatment group. Comparative analyses will consider also the ACE inhibitor and the ARB arms. No sample size, however, is calculated for this comparison.

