Statistical analysis will be performed according to the intention-to-treat principle. Statisticians and investigators involved in statistical analyses will be blinded to the treatment assignments of the subjects. Primary end point is time to progression to microalbuminuria. At variance with end points such as ‘death’ or ‘dialysis’, the microalbuminuric state does not allow a clear cut recognition of the exact occurrence date, but, rather, two dates can be identified: the last time the patient is found to be normoalbuminuric and the first time the patient is detected as microalbuminuric. This kind of end point gives rise to interval censored data. The interval censoring method will take into account that the ‘true’ date of microalbuminuria development lies within this interval. The primary analysis will be performed by means of the accelerated failure time model, implemented in SAS PROC LIFEREG, which allows direct incorporation of interval censored data, and by use of proportional hazards model, implemented in SAS PROC PHREG. The following baseline covariates will be included in the model: site, age, gender, smoking habits (never vs. current and former), a measure of blood pressure and log transformed urinary albumin excretion. Kaplan-Meier curves will also be plotted, using the midpoint of the interval as event time. One interim analysis will be undertaken on the intention-to-treat population, when about 50% of total information is expected to be collected. The method of O’Brien and Fleming will be used to determine for statistical significance at the interim evaluation, that would constitute grounds to recommend trial termination. This threshold will be a P value of 0.0054 (nominal significance level) or less in order to ‘preserve’ an overall 5% level of significance. A further evaluation will take place at the end of the enrolment period for the purposes of possible adaptation of the sample size or observation period in order to achieve adequate power. Other details regarding the statistical approaches will be supplemented by a detailed plan which will be prepared after release of the protocol but before the start of the clinical part of the study. Should new evidence come to light as a result of running other trials before this trial is analyzed or should new methods of analysis become available in the statistical literature, or should the trial be affected by unforeseen circumstances, it may be necessary to modify the analysis plan.

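### Patients taken off study drug for unresolved hypotension or hyperkalaemia also leave the study, so the intention-to-treat analysis lacks their later outcomes

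*Protocol*

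**What the plan says.** Study Design and Treatment allows back-titration, first of concomitant treatments and then of study drugs, for symptomatic hypotension or severe hyperkalaemia. It continues: "If the above clinical or laboratory abnormalities will not recover despite back-titration, the study drugs will be withdrawn". The next sentence ends participation: "The patients will be monitored until full recovery of the event and, however, for at least two weeks and then withdrawn from the study".

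Statistical Analysis states: "Statistical analysis will be performed according to the intention-to-treat principle". The primary endpoint is time to microalbuminuria with interval censoring: "The primary analysis will be performed by means of the accelerated failure time model", together with a proportional hazards model. The interim efficacy analysis is also on the intention-to-treat population.

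Safety Variables lists abnormalities "such as acute hypotension, cough, acute renal function deterioration or hyperkalemia) possibly related to the study drugs". Both triggers for leaving the study are of a kind named there.

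Sample Size requires 179 completers per group and, "to account for a 5% drop-out rate, 188 patients per group should be included".

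Nothing else restores outcome follow-up. The adverse event section (Collection/Registration of Information) follows patients only until the event resolves, is explained, or ends in death. The Appendix 1 schedule marks permanent discontinuation and a trial end summary as optional at the same treatment visits, which fits leaving the trial when drug is stopped.

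**The concern.** An intention-to-treat comparison needs outcomes for everyone randomised, whether or not they stay on drug. Here the protocol itself orders follow-up to end for a group defined by a possible drug reaction. These patients remain in the analysis set, but they are censored when they leave. Both planned models treat that censoring as unrelated to future risk.

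If drug is stopped, whatever benefit the assigned treatment gave may stop with it, and the censored data cannot show this. The result drifts towards the effect while on drug but carries the intention-to-treat label. The same applies to cardiovascular events, a secondary outcome, and to the interim efficacy test.

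This is a rule about data collection. A SAP can define an estimand or a sensitivity analysis, but it cannot recover urine collections and events that were never recorded.

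**Working it through.** **1. The plan's own figure.** Inputs from Sample Size: 27% versus 14.85%, two-sided 5%, 80% power. The pooled two-proportion formula is

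n = [1.96·√(2·p̄·(1−p̄)) + 0.8416·√(p₁(1−p₁) + p₂(1−p₂))]² / (p₁−p₂)², with p̄ = 0.20925.

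This gives (1.1275 + 0.4787)² / 0.1215² ≈ 175 per group, against 179 stated (within 3%). Then 179 × 1.05 = 188 and 3 × 188 = 564. The point does not rest on an arithmetic error.

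**2. Loss of numbers.** The 5% allowance has to cover these mandated exits as well as ordinary losses. If everyone withdrawn is treated as lost from 188 per group, power is 0.809 at 5% (178.6 left), 0.787 at 10% (169.2) and 0.764 at 15% (159.8). That loss is modest; the larger issue is what is being estimated.

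**3. Illustration of the gap.** From the protocol: 6% per year on benazepril and 4.5 years. The planned 45% reduction is taken as an on-drug hazard ratio of 0.55. Assumed, because the documents do not say: the withdrawn fractions; an off-drug hazard of m = 1 to 2 times the benazepril hazard; and withdrawn patients otherwise at the same risk as the rest.

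Event-free proportions at 4.5 years:

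- benazepril, on drug throughout: exp(−0.27) = 0.7634
- combination, on drug throughout: exp(−0.55 × 0.27) = 0.8620
- off drug throughout: exp(−0.27m) = 0.7634 (m = 1) or 0.5827 (m = 2)

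For withdrawn fraction w in an arm, S = (1−w)·S_on + w·S_wd. The treatment-policy hazard ratio is taken as ln S(combination) / ln S(benazepril).

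- *All withdrawals at time zero:* S_wd is the off-drug value.
- *Withdrawals spread uniformly over follow-up:* S_wd = (S_on − S_off) / ((h_off − h_on) × 4.5). For the combination this is (0.8620 − 0.7634)/0.1215 = 0.812 (m = 1) or (0.8620 − 0.5827)/0.3915 = 0.713 (m = 2). For benazepril it is 0.763 or 0.669.

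Worked case, 5% in both arms, time zero, m = 1: the combination has 0.95 × 0.8620 + 0.05 × 0.7634 = 0.8571 and benazepril has 0.7634. The ratio is 0.1542/0.27 = 0.571. With m = 2 the proportions are 0.8480 and 0.7543, and the ratio is 0.585.

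| Withdrawn, combination vs benazepril | Uniform over follow-up (m = 1 to 2) | All at time zero (m = 1 to 2) | Censored data |
|---|---|---|---|
| 5% vs 5% | 0.561 to 0.569 | 0.571 to 0.585 | 0.55 |
| 10% vs 5% | 0.572 to 0.601 | 0.593 to 0.644 | 0.55 |
| 15% vs 5% | 0.583 to 0.633 | 0.614 to 0.703 | 0.55 |

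A constant hazard of 0.06 gives 23.7% at 4.5 years, because the protocol's 27% is the linear product 6% × 4.5. Setting the hazard to reach exactly 27% (−ln 0.73/4.5 = 0.0699) changes little: the most extreme cell becomes 0.699 instead of 0.703.

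**The case against.** Several points on the other side stand.

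- **The trigger is narrow.** Patients leave only if the abnormality persists after back-titration. The protocol allows 5% drop-out in total, about 9 patients per group (0.05 × 188 = 9.4). The 10% and 15% rows put the combination arm at two to three times that whole allowance.
- **Timing matters.** The larger gaps need every withdrawal to occur at time zero. Spread over follow-up, the 5% case moves the hazard ratio by only about 0.01 to 0.02.
- **Unequal loss by arm is not documented.** A reader might infer that dual blockade must lose more patients. Every arm receives renin-angiotensin blockade, the combination uses halved doses, up-titration depends on tolerance in all arms, and no rate by arm is given. Unequal rates are an assumption.
- **The passages do not make intention-to-treat logically impossible.** Patients can still be analysed as randomised with data up to censoring, and they contribute person-time before they leave. So the estimate is also not simply the effect in those who tolerate the drugs. The defect is missing outcome data.
- **The illustration does not demonstrate informative censoring.** Withdrawn patients are given the same on-drug risk as the rest, so 0.55 in the censored data follows by construction. The table measures the gap between an on-drug and a treatment-policy effect. Informative censoring is plausible, given that the triggers may be drug-related, but it is not quantified.

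None of this supplies the missing follow-up. The rule is explicit, and no other section overrides it.

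**Conclusion.** The concern holds in this limited form: the protocol orders follow-up to stop for a group whose outcomes its intention-to-treat analysis needs, and the resulting estimate leans towards an on-treatment effect. With the protocol's 5% allowance applied to both arms, the illustrated difference is about 0.01 to 0.035 on the hazard ratio scale. It reaches about 0.15 only with 15% versus 5% withdrawn, all at the start, and a doubled off-drug hazard. These sizes rest on assumed withdrawal rates, timing and off-drug hazards. Neither the true size nor the direction of bias can be derived from the documents. What makes it worth correcting is that the lost data cannot be recovered at analysis and the remedy is small.

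**What to change.** Reconcile Study Design and Treatment with Statistical Analysis by separating the end of study drug from the end of follow-up. Replace the closing clause that takes these patients out of the study with wording such as: after study drug is stopped, patients continue scheduled visits, overnight urine collections and event reporting until study end, unless they withdraw consent.

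Analyse them as randomised with all collected data, and keep censoring at drug discontinuation as a sensitivity analysis. Align the Appendix 1 trial end summary so that permanent discontinuation does not by itself close a patient's record.

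Nothing here alters when study drug is stopped or what care follows. The sponsor should state whether the protocol's restrictions on concomitant drugs still apply to these patients.

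Cost: a protocol amendment, which the Legal and Ethical Aspects section requires to be submitted to the Ethics Committee; notice to sites; and the scheduled visits and collections for what is probably a small number of patients.
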